**Depression outcomes**													
Hamilton depression rating scale	17	X	X				X		X	X	X	X	CI
Quick inventory of depression symptomatology	16		X	X	X	X	X	X	X	X	X	X	PQO
Clinical global impressions scale	2		X				X		X	X	X	X	CI
SCID mood module for major depression	-								X	X	X	X	CI
Longitudinal interval follow-up evaluation	-								X	X	X	X	CI
**Functional status outcomes**													
Health status-short form 12	12		X				X		X	X	X	X	PQO
Work and social activity scale	5		X				X		X	X	X	X	PQO
Quality of life enjoyment satisfaction questionnaire	15		X				X		X	X	X	X	PQO
**Measures of mediation/moderation**													
Therapeutic rationale scale	4				X				X				PQO
State trait anxiety inventory	40		X				X		X	X	X	X	PQO
Perceived stress scale	14		X				X		X	X	X	X	PQO
Childhood trauma questionnaire		X											PQO
Ruminative response scale	22		X				X		X	X	X	X	PQO
Acceptance and avoidance questionnaire	10		X				X		X	X	X	X	PQO
Five facet mindfulness questionnaire	30		X				X		X	X	X	X	PQO
Experiences questionnaire	20		X				X		X	X	X	X	PQO
Self-compassion scale	26		X				X		X	X	X	X	PQO
Medication/Psychotherapy change form	-		X	X	X	X	X	X	X	X	X	X	CI
Homework summary log	-		X		X	X	X	X	X	X	X	X	PQO

*CI = Clinical interview; PQO = Patient questionnaire online.

Data obtained during the intake interview was presented in a weekly research conference where the principal investigator reviewed eligibility criteria on a case-by-case basis to make determinations about participants’ eligibility for enrollment.

### Randomization and baseline assessment

The unit of randomization was the patient, and randomization tables were stratified by gender to ensure balanced assignment. Patients were randomized during the baseline assessment, which occurred within two weeks of the commencement of treatment (see Figure 1. Study Design and Participant Flow). Baseline assessments served two purposes: 1) to ensure that patients continued to meet eligibility criteria for MDD with scores ≥ 14 on the HAM-D and 2) to serve as the primary data collection point (see Outcome Measures section). Patients who reported improved depressive symptoms during the baseline interview with HAMD total scores < 14, were not randomized to treatment and told that they could be reassessed for a future intervention cohort should their depression symptoms relapse. Participants who continued to be eligible on measures of depressive severity were then randomly assigned to either MBCT + TAU or HEP + TAU.

**Figure 1 F1:**
[figure not shown]
Study design of randomized control trial of Mindfulness-Based Cognitive Therapy (MBCT) versus the Health-Enhancement Program (HEP) in adults with treatment-resistant depression.

### Outcome measures

Outcomes were assessed at baseline, weeks 1–7, at the end of treatment (week 8) and at weeks 24, 36 and 52 during the long-term follow-up phase. Data was obtained from patient questionnaires completed online and through clinical RA ratings, which were confirmed with chart review of medical records when necessitated.

### Primary and secondary outcome measures

The primary outcome measurement was improvement of depression severity after 8 weeks, as measured through change in HAM-D total scores from pre- to post-treatment, treatment response (scores ≥ 50% decrease from baseline) and remission (post-treatment scores ≤ 7). Length of treatment efficacy, a secondary outcome, was assessed up to 1 year after baseline using HAM-D scores, response and remission rates by measuring rate of depression relapse using the semi-structured Longitudinal Interval Follow-up Evaluation (LIFE) [35]. The participant-rated 16-item Quick Inventory of Depressive Symptomatology (QIDS) [36] was used as a secondary measurement to assess change in depressive severity, response (scores ≥ 50% decrease from baseline) and remission (scores ≤ 5) during the same treatment and follow-up time period.

Functional status and quality of life were additional secondary outcomes measured using the SF-12 Health Survey [37,38], the Work and Social Adjustment Scale (WSAS) [39], [40] and the Quality of Life, Enjoyment, and Satisfaction Questionnaire (Q-LES-SQ) [41].

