**Methods/Design:**

The purpose of this study was to evaluate whether MBCT is an effective augmentation of antidepressants for adults with MDD who failed to respond to standard pharmacotherapy. MBCT was compared to an active control condition, the Health-Enhancement Program (HEP), which incorporates physical activity, functional movement, music therapy and nutritional advice. HEP was designed as a comparator condition for mindfulness-based interventions to control for non-specific effects. Originally investigated in a non-clinical sample to promote stress reduction, HEP was adapted for a depressed population for this study. Individuals age 18 and older with moderate to severe TRD, who failed to respond to at least two trials of antidepressants in the current episode, were recruited to participate. All participants were taking antidepressants (Treatment as usual; TAU) at the time of enrollment. After signing an informed consent, participants were randomly assigned to either MBCT or HEP condition. Participants were followed for 1 year and assessed at weeks 1–7, 8, 24, 36, and 52. Change in depression severity, rate of treatment response and remission after 8 weeks were the primary outcomes measured by the clinician-rated Hamilton Depression Severity Rating (HAM-D) 17-item scale. The participant-rated Quick Inventory of Depression Symptomology (QIDS-SR) 16-item scale was the secondary outcome measure of depression severity, response, and remission.

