### Sample size

To estimate sample size, effect sizes were based on outcomes from previous studies and our pilot data [15,21-24]. In a review of 21 mindfulness-meditation interventions, Baer [23] found an average effect size of .90 for depressive symptom reduction. In examining the relapse rates of individuals receiving MBCT versus TAU, Teasdale et al. [14] found an effect size of .59 and Ma et al. [15] of .88 for participants with a history of 3 or more depressive episodes. Our pilot data indicated an average effect size of 1.13, which compared similarly to Kenny’s effect size of 1.03 in a TRD population [12]. Finucane et al., working with a more severely depressed population, found an effect size of 1.54 [25]. Kingston et al. found an effect size of 1.07 in reducing depression in psychiatric outpatients [26]. There were no significant differences in effect on depression in a comparison of HEP and MBSR [19,20]. Using the formula provided by Donner and Klar [27], we estimated sample sizes to detect response to the intervention (MBCT + TAU would be superior to HEP + TAU on depression outcomes). Results indicated sample sizes ranging up to approximately 50 per condition. A total sample of 124 participants were regarded as necessary to provide 80% power to detect a moderate effect size in the face with an estimated attrition of approximately 20%, similar to our rates of attrition in clinical MBCT groups.

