### Planned analytic approach

The primary outcome measure of the HAM-D will be compared between participants randomized to the MBCT + TAU and the HEP + TAU groups using a mixed-effects statistical model [58,59]. Mean levels of severity, and response and remission rates at week 8 and bivariate measures will be compared between treatment conditions using logistic regression models with generalized estimating equations to correct for interdependence resulting from group membership. The secondary outcome measures of the QIDS-SR and CGI will be compared using the same methodology but replacing the HAM-D with the QIDS-SR and CGI severity measures. We will also assess relapse occurrence in both arms using the LIFE interview at weeks 24, 36 and 52.

The efficacy of MBCT + TAU versus HEP + TAU on functional status as a secondary outcome will be assessed using similar models to the methods used to test the reduction in HAM-D_17_ scores. For each of the four scales, scores at week 8 will be compared between randomized conditions using a mixed-effects statistical model, which will include effects for randomized condition, therapy group and baseline disability score. The test of the estimated parameter for treatment condition will be a direct test of this hypothesis. Mediating effects of the relationship of treatment assignment with outcome will be tested using a series of linear regression models. Putative mediators, enhanced mindfulness (FFMQ), enhanced self-compassion (SCS), diminished rumination (RRS) and decreased experiential avoidance (AAQ) will be assessed at weeks 4, 8, 24, 36, and 52. We will also assess persistence of treatment changes in depression (HAM-D, QIDS-SR, CGI), functional status (SF-12, WSAS, Q-LES-Q-SF), mindfulness (FFMQ), rumination (RRS), self-compassion (SCS) and avoidance (AAQ) at weeks 24, 36 and 52 by analyses parallel to those outlined for testing Hypotheses 1 and 2 using data from the weeks 24, 36, and Week 52. Mixed-effects and logistic regression models using a generalized estimating equation (GEE) will allow direct testing of these effects. Moderating factors (e.g. age of depression onset, prior poor treatment outcomes, co-morbid psychiatric diagnoses and other socio-demographics) associated with TRD will also be included in the model.

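### Three overlapping week-8 HAM-D measures share primary status with no ranking or success rule, and mean severity is also assigned to a logistic model

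*Protocol article*

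**What the plan says.** Three places in the protocol article bear on this.

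- **Abstract, Methods/Design** uses the plural: "Change in depression severity, rate of treatment response and remission after 8 weeks were the primary outcomes".
- **Primary and secondary outcome measures** uses the singular, "The primary outcome measurement was improvement of depression severity after 8 weeks, as measured through change in HAM-D total scores from pre- to post-treatment", but continues the same sentence with "treatment response (scores ≥ 50% decrease from baseline) and remission (post-treatment scores ≤ 7". One primary outcome is thus defined by three measures.
- **Planned analytic approach** opens with "The primary outcome measure of the HAM-D will be compared between participants randomized to" the two arms by a mixed-effects model, without saying which of the three measures is meant. The next sentence reads: "Mean levels of severity, and response and remission rates at week 8 and bivariate measures will be compared between treatment conditions using logistic regression", with GEE to allow for therapy-group membership.

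The Sample size section does not settle the matter. It plans 124 participants "to provide 80% power to detect a moderate effect size", gives that effect no number, and ties it to depression outcomes in general. The article states no significance level or sidedness. No SAP is at hand.

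**The concern.** With three primary measures and no success rule, a split result has no pre-stated reading. If response were significant and mean change were not, one reader could call the trial positive and another negative, and both could cite the article. If any single success is enough, the chance of a false claim exceeds the level of each separate test. If all three are needed, the trial has less power than the single-effect calculation suggests.

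The extra measures add little information. Response and remission are both cut from the score that gives the mean change.

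The logistic sentence is a different problem. It gives one continuous outcome two stated models, and the second does not suit that type of outcome.

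**Working it through.** **1. The article's own figure.** About 50 per condition with 20% attrition gives 100 / 0.80 = 125 in total, or 50 / 0.80 = 62.5, rounded to 63 per arm (126). Both are within 2 of the stated 124. In reverse, 124 × 0.80 = 99.2 completers, or 49.6 per arm. With 50 per arm and an assumed two-sided 0.05, the effect detectable with 80% power is (1.960 + 0.842) × √(2/50) = 0.56 SD, ignoring clustering. This is a calculation for one test. It makes no allowance for three.

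**2. Overlap.** Randomization and baseline assessment requires HAM-D ≥ 14. A week-8 score ≤ 7 is then at most 7/14 = 50% of baseline, which meets the response definition. Remission is therefore a subset of response.

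**3. Limits for the any-one-wins rule.** Assume two-sided 0.05 per test.

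- Independent tests: 1 − 0.95³ = 14.3%. The Bonferroni bound is 3 × 0.05 = 15%.
- Equally correlated normal test statistics (1,000,000 draws):

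| Assumed correlation | At least one significant |
|---|---|
| 0 | 14.3% |
| 0.5 | 12.6% |
| 0.7 | 10.9% |
| 0.8 | 9.8% |
| 0.9 | 8.3% |

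**4. Null simulation on the HAM-D scale.** All distributional inputs are assumptions, since the article gives none. Baseline has mean 18 and SD 3, with a floor of 14. The mean proportional fall is 20% to 50%, with SD 30% to 40%. There are 50 or 62 per arm and 20,000 trials per scenario. Mean score is tested by ANCOVA, and response and remission by Wald tests of the log odds ratio. Therapy-group clustering is not modelled. Response ranged from 21% to 52% and remission from 14% to 40%, and the test statistics correlated at about 0.6 to 0.8 in absolute size.

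- At least one significant result, either direction: 9.6% to 10.7%.
- At least one significant result favouring MBCT: 4.8% to 5.4%, against a nominal 2.5%.

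A separate null simulation gave 8.6% to 10.0% and 4.5% to 5.1%. Another used an assumed week-8 mean of 12, SD 6 and baseline correlation of 0.35, and gave 10.2% (50 per arm) to 10.5% (62 per arm). Together these support about 9% to 11% in either direction.

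**5. The all-must-win rule.** Error is then no higher than for one test, but joint power cannot exceed that of the weakest test. Under the last set of assumptions, a 0.5 SD shift (response 30% against 49%) with 50 per arm gives 69% power for the mean and 49% for response. Power to win on all three is then at most 49%.

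**6. The model assignment.** Logistic regression models a binary outcome. Response and remission fit that description and mean severity does not. The preceding sentence has already assigned the HAM-D to a mixed-effects model.

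**The case against.** The strongest reply is that ranking outcomes and dividing alpha are commonly left to an SAP or full protocol, and neither is shown. That stands for missing detail: a hierarchy may exist elsewhere. It does not cover what the article states. The article gives three measures primary status and assigns their analyses, one of them wrongly, and any ranking elsewhere would have to be reconciled with this text.

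It can also be said that the analysis section puts a single HAM-D measure first, under a mixed-effects model, and only then turns to response and remission. This suggests a lead analysis but does not state one, and the Abstract says otherwise.

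Three objections to the size of the problem stand:

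- The hypothesis is directional, since the Sample size section expects MBCT to be superior. A figure near 10% includes false results favouring HEP. For a false MBCT win the rate is about 5%.
- The article states no alpha, so no figure of its own is contradicted. Two-sided 0.05 per test is an assumption.
- The inflation exists only if any one success counts, and the article does not say so.

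The logistic wording may be compressed drafting, because a later sentence in the same section names mixed-effects and logistic models together. It still needs correcting.

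**Conclusion.** The point holds in two separate parts. First, primary status is given to three overlapping measures without a ranking or a success rule, and the three sections word it differently. Second, mean severity is assigned to a model that cannot analyse it.

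Under an any-one-wins rule with an assumed two-sided 0.05 per test, the chance of at least one false-positive primary result is about 9% to 11% for plausible assumed score distributions, and 8% to 14% over assumed correlations from 0.9 to 0. Counting only results that favour MBCT, it is about 5% against 2.5%. The inflation is roughly twofold on either count.

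A reader might infer that the trial's false-positive rate is simply 10% instead of 5%. The article does not support that, because it states neither the level nor the rule that the figure needs. A reader might also infer that the logistic sentence causes the inflation. It does not: the figures come from testing three outcomes.

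**What to change.** - Name the between-arm difference in week-8 HAM-D total score, from the linear mixed-effects model, as the single primary test at two-sided 0.05.
- Make response and then remission key secondary outcomes in fixed sequence, each tested only if the one before is significant. Family-wise error then stays at 5%.
- Use the same designation in the Abstract, in Primary and secondary outcome measures, and in Planned analytic approach.
- Take mean severity out of the logistic sentence and limit logistic GEE to the binary outcomes.

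Holm's procedure over the three is a valid alternative, but its first step uses 0.05 / 3 = 0.0167. For comparison, a plain Bonferroni split at that level would cut power from 80% to about 66% at 0.56 SD with 50 completers per arm. The fixed sequence leaves the primary test at full strength.

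The follow-up comparisons need no relabelling, since efficacy up to one year is already called secondary.

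The cost is about one paragraph and no extra participants. The analyses are written in the future tense, so the change should be made before outcomes are compared by arm. The small downside is that response or remission alone could no longer carry the primary claim.

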#### Mediators, moderators and potential covariates

A number of other psychometric variables believed to be associated with mindfulness were investigated and measured at baseline, during mid-point (week 4), after the end of treatment (week 8) and the long-term follow-up weeks 24, 36, and 52. The following potential mediators related to MBCT were measured: mindfulness with the Five Facet Mindfulness Questionnaire [42]; experiential avoidance with the Acceptance and Action Questionnaire (AAQ) [43]; rumination with the Ruminative Response Scale (RRS) [44,45]; and self-compassion with the Self-Compassion Scale (SCS) [46].

Psychiatric factors that may impact depression severity and resistance such as early age of depression onset, number of recurrences, poor treatment outcomes (e.g. incomplete remission) and co-morbid psychiatric illness (e.g. anxiety disorders [47] or personality disorders [48]), will be included in the analysis as covariates [49]. Also included will be other factors known to be moderators of depression treatment outcomes. These include demographic factors such as minority status, ethnicity and lower socio-economic status [50] and stress, both current [51,52] and a childhood history of stress [53] (trauma, abuse, neglect) which were collected during the baseline assessment.

Medication changes in the TAU arm are the same ones utilized in treating persisting or worsening depression in the STAR*D studies [3,8]. Changes were tracked during the 8-week treatment and over the 52 week follow-up through patient report and chart review. Alternate forms of treatment (i.e. individual psychotherapy, group psychotherapy, electroconvulsive therapy, etc.) for depression was tracked after the treatment-phase of the study through patient report and interview. These treatments will be analyzed as covariates as well as secondary outcomes, similar to the aforementioned medication changes.

Treatment expectancy to assess potential moderating effects of positive expectancy was measured through the Treatment Rationale Scale [54-56], which participants completed after the first and final sessions (weeks 2 and 8). Changes in psychotropic medications including antidepressants, benzodiazepines and mood stabilizers were tracked at every assessment time point using a medication evaluation form. Lastly, participant engagement in treatment was measured through attendance and total time spent completing homework and related activities outside of class. A complete list of the outcome measures, measurement points and assessment methods for the study are summarized in Table 4.

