## Methods/Design

This study is a single-site, randomized, controlled clinical trial of MBCT augmentation of Treatment-as-Usual (MBCT + TAU) and HEP augmentation of TAU (HEP + TAU). TAU consisted of standard medication management for depression. In a single-blind fashion, participants were aware of treatment allocation but were blind to study hypothesis. Research assistants (RA’s) responsible for assessment of depression severity, were blind to individual randomization assignments. See Table 1 for a list of inclusion and exclusion criteria.

**Table 1 T1:** Components of Mindfulness-Based Cognitive Therapy (MBCT) and the Health-Enhancement Program (HEP)

**Factor**	**MBCT**	**HEP**
Manualized intervention	X	X
Mindfulness training	X	
Music therapy		X
Nutrition education		X
Group support	X	X
Therapeutic attention	X	X
Session time (135 minutes)	X	X
Session duration (8 weeks)	X	X
Physical activity	X (e.g. yoga)	X (e.g. exercise, stretching)
Functional movement		X
Time equivalent homework	X	X
Facilitator buy-in to method	X	X

*Note.* X indicates the presence of each component in the intervention.

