## Discussion

Treatment-resistant depression is a condition associated with high rates of disability, chronicity, reoccurrence and failed response to antidepressant treatment [3,8]. Through decreased workforce productivity and disability, the economic burden caused by refractory depression is enormous [10,61]; hence the importance of finding effective treatment modalities for this population is clear and of vital public health interest. This investigation represents the first RCT to evaluate MBCT for TRD. Results from this study will address whether MBCT is superior in reducing depression severity after 8 week treatment and improving relapse and remission rates over time in comparison to a credible comparator condition, developed to control for non-specific treatment effects. If successful, this study will identify an augmentation treatment for a large, hard-to-treat population for whom few treatments have been effective.

After analysis, we will be able to assess whether the specific constructs of a mindfulness-based intervention, such as the putative mediators in MBCT (increased mindfulness, self-compassion and decreased rumination and experiential avoidance) are enhanced more after an 8-week treatment with MBCT compared with HEP, and whether they are associated with positive treatment outcomes. We will also be able to evaluate whether treatment gains between groups (i.e. reduced depression severity, increased functional status) are retained during a 1-year follow-up and whether differential effects might be mediated by the specific constructs of MBCT listed above. Finally, we will be able to assess whether participant expectancy, treatment adherence (i.e. number of sessions attended), and compliance (i.e. number of minutes of homework completed) predicted treatment outcomes.

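### Treatment expectancy is named as a moderator but is rated only after randomisation and the start of treatment, so a treatment-by-expectancy test can show moderation that is not there

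*Protocol article*

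**What the plan says.** All references are to the protocol article.

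- **Role.** Mediators, moderators and potential covariates: "Treatment expectancy to assess potential moderating effects of positive expectancy was measured through the Treatment Rationale Scale".
- **Timing.** The same sentence describes a scale "which participants completed after the first and final sessions (weeks 2 and 8".
- **Schedule.** Table 4, under the measures of mediation and moderation, lists the "Therapeutic rationale scale" (evidently the same instrument under a slightly different name). It is marked at weeks 2 and 8 only.
- **Randomisation.** Randomization and baseline assessment: "Patients were randomized during the baseline assessment, which occurred within two weeks of the commencement of treatment".
- **Knowledge of arm.** Methods/Design: "participants were aware of treatment allocation but were blind to study hypothesis".
- **Primary time point.** Primary and secondary outcome measures: "The primary outcome measurement was improvement of depression severity after 8 weeks", which is also the week of the second expectancy rating.
- **Second use.** The Discussion expects to assess whether "participant expectancy, treatment adherence (i.e. number of sessions attended), and compliance (i.e. number of minutes of homework completed) predicted treatment outcomes".

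The Planned analytic approach says that moderating factors linked to TRD go into the model. Its examples are age at onset, earlier poor treatment outcomes, comorbid diagnoses and socio-demographic factors. Expectancy is not among them.

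**The concern.** A moderator analysis asks whether the MBCT versus HEP effect differs between kinds of patient. That question is meaningful only if a patient would have been the same kind of patient in either arm, so the variable must not be open to influence from the arm. An expectancy rating given after allocation is known and a class has been attended does not meet that condition. It may reflect the arm, the first impression of the class, or early change in mood.

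The article treats its other moderators differently: the demographic and stress factors were collected at baseline. Its Limitations section also makes clear that the construct of interest is what patients believed at the outset, and neither rating captures that.

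The interpretation of the trial is at stake. HEP was chosen to control for non-specific effects, and expectancy is an obvious rival explanation for any difference. A spurious interaction could be read as showing for whom MBCT works, when it shows only that ratings followed improvement more closely in one arm.

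**Working it through.** **1. Order of events.** Baseline assessment and randomisation come first. Patients then know their arm. Treatment starts within two weeks, the first rating follows the first session (week 2 in Table 4), and the second rating falls in week 8. Both ratings come after randomisation and exposure, and no pre-randomisation rating exists.

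**2. The plan's own figure.** The article gives no figure on this point, so there is none to reproduce. It also gives no arm difference in expectancy and no correlation with outcome. Every effect size below is an assumption.

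**3. Illustrative simulation.** There were 4,000 trials per setting, with N = 100 (about 50 per arm) and N = 124, both sizes taken from the Sample size section.

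- Improvement = 0.5 × arm + 0.6 × U + 0.8 × noise, where U is unmeasured prognosis. The outcome SD within arm is √(0.36 + 0.64) = 1. The true arm effect is 0.50 SD for every patient, so there is no true moderation.
- Week 2 rating = 0.5 × arm + 0.8 × noise + b × U. Equal tracking has b = 0.5 in both arms. Unequal tracking has b = 0.1 in HEP and 0.7 in MBCT.
- Pre-randomisation rating = noise + 0.5 × U.
- Week 8 rating = 0.3 × arm + 0.8 × noise + c × improvement, with c = 0.2 in HEP and 0.7 in MBCT.
- Fitted model: arm, standardised rating, and their product.

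| Setting | False interaction, N = 100 | False interaction, N = 124 | Arm coefficient with rating in model |
|---|---|---|---|
| Rated before randomisation | 5.2% | 5.6% | 0.50 |
| Week 2, equal tracking | 5.4% | 5.6% | 0.33 |
| Week 2, unequal tracking | 26.2% | 29.6% | 0.39 |
| Week 8, rating follows outcome more in MBCT | 38.8% | 46.5% | 0.20 to 0.21 |

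Without the rating in the model, the arm coefficient is 0.50 in every setting. The simulation standard error at 5% is √(0.05 × 0.95 / 4,000) = 0.34 percentage points, so 5.2% to 5.6% is compatible with the nominal level.

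**4. Check by hand (week 2).** The slope of improvement on the rating within an arm is 0.6b / (0.8² + b²).

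- Unequal tracking: HEP 0.06 / 0.65 = 0.092; MBCT 0.42 / 1.13 = 0.372; difference 0.279 per raw unit. The pooled rating variance is (0.65 + 1.13)/2 + 0.25² = 0.9525, SD 0.976. The standardised difference is 0.279 × 0.976 = 0.27, against simulated mean interactions of 0.274 and 0.269.
- Equal tracking: both slopes are 0.30 / 0.89 = 0.337, so the interaction is zero. The adjusted arm effect is 0.5 − 0.337 × 0.5 = 0.33, against 0.329 and 0.334.

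False moderation therefore comes from unequal tracking. A simple shift in expectancy between arms does not inflate the interaction test. It moves the arm coefficient only if the rating is put in that model.

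**The case against.** The strongest reply is that this is an exploratory analysis with no specified model, in an article that condenses a longer protocol, and that a credibility rating is sensibly taken once the rationale has been presented. The second part stands: the first rating is a reasonable measure of process and of comparator credibility. The first part does not remove the point, because the article states both the role and the timing, and the two are incompatible.

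Several stronger readings are tempting, and the documents do not support them.

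- **The trial's treatment effect is biased.** No section puts expectancy in the primary HAM-D model or in any other model estimating the arm effect. The lists of covariates, moderators and added indicators in the Mediators section and the Planned analytic approach omit it. The lower arm coefficients in the table apply only if someone adds it.
- **The week 8 rating will be used to explain the week 8 HAM-D.** The article records when the rating is taken, not that use. The rating also precedes the follow-up at weeks 24, 36 and 52. The week 8 row of the table shows why that use should be ruled out, not that it is planned.
- **Attendance and homework are misused in the same way.** The article describes them as engagement measures and possible predictors, not as moderators.
- **A false moderation finding is likely.** The 26% to 30% needs tracking seven times stronger in one arm (0.7 versus 0.1). HEP was designed to match MBCT in credibility. Equal average credibility does not guarantee equal tracking, but if tracking is equal the test keeps its level.

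**Conclusion.** The point holds in limited form. Expectancy as measured is a post-randomisation variable, so the stated moderator analysis cannot answer the question put to it. This follows from the timing alone and needs no assumption.

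The size of the harm is conditional. The false-positive rate of the interaction test is about 26% to 30% under the assumed strongly unequal tracking at week 2, and about 5% under equal tracking. The documents give nothing to place the trial between these.

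The unadjusted primary comparison is untouched. The consequence is confined to a secondary claim about expectancy, though one that bears on how the comparison with HEP is read.

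**What to change.** Change the analysis wording as follows.

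1. Do not analyse expectancy as a moderator. State that no pre-randomisation rating exists, and limit moderator tests to variables measured at screening or week 0.
2. Use the first rating for a between-arm comparison of credibility. If wanted, also use it as a labelled process or mediation variable, with the assumptions of that analysis stated.
3. Do not use the week 8 rating to moderate or predict the week 8 outcome.
4. Do not add either rating as a covariate in the models that estimate the MBCT versus HEP effect.
5. Report the associations of expectancy, attendance and homework with outcome, as listed in the Discussion, without a causal reading.

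Recruitment closed in September 2013, so a baseline rating cannot be added. The analyses are still described in the future tense, so the wording can change. The cost is the planned expectancy-moderation claim, which these data cannot support; no data collection or sample size is affected.
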